##### Acceptability of Olyset®Plus ceiling nets

Focus group discussions (FGDs), a structured questionnaire, and in-depth interviews will be used to assess the acceptance of the Olyset®Plus ceiling nets. At the end of the 12-month follow-up, all cohort members will be subjected to the structured questionnaire, and a part of them will be invited to in-depth interviews based on their responses to the questionnaires.

#### Plans to promote participant retention and complete follow-up {18b}

To promote retention among participants in the control arm, we will install ceiling nets in their houses after the 12-month follow-up period, irrespective of the study outcome. This arrangement was agreed upon by CHVs and village leaders as an acceptable study incentive, conveyed to potential study participants during community sensitization, and reiterated to participants during the census survey and informed consent process.

In the cohort survey, CHVs will make an appointment with participants and confirm their available date and time before each bi-weekly home visit. Participants will receive a small remuneration (i.e., rice, beans, cooking oil, and soap) when they provide a venous blood sample. CHVs will be instructed to relay to the research team any issue raised by cohort participants, and discussions will be held to resolve issues that cannot be immediately addressed. The research team will periodically accompany the CHVs in their home visits to reinforce to cohort participants the importance of the study.

#### Data management {19}

Study data will be collected on Android-based tablet computers using the REDCap application to promote data quality and security. Data validation, such as range checks and completeness checks, will be enabled in all survey instruments. For cross-sectional surveys, data will be uploaded to the REDCap server at Mount Kenya University at the conclusion of each survey day. After the data manager confirms the data quality on the server, data stored locally on the tablet computers will be deleted before the next survey to avoid potential overwriting of existing data. Survey data will be uploaded to the REDCap server at least once a week for the longitudinal cohorts. Each cohort participant is given a unique identifier, and each visit is preprogrammed as a defined event in the REDCap data collection instrument to facilitate data entry. Cohort surveys will be conducted by CHVs familiar with cohort participants and will be prompted to confirm the identity of the cohort participants before data entry. In addition, the data manager will confirm the data quality on the server once a week.

Access to survey data will be limited to data analysts and the data manager in the research team. In addition, personally identifiable information will be removed before data analyses.

#### Confidentiality {27}

To maintain confidentiality, each participant in cross-sectional surveys and the longitudinal cohort is assigned a unique identifier. The data collected will be labeled using the unique identifier and stored separately from the key linking personal information (name, date of birth, GPS, and phone number). The data will be kept on a secure server that is only accessible to the research staff. Publications will contain only aggregated data, and no personal information will be included.

#### Plans for collection, laboratory evaluation, and storage of biological specimens for genetic or molecular analysis in this trial/future use {33}

Blood samples will be collected to examine malaria infections by multiple methods, hemoglobin levels, immunity against malaria parasites and mosquito saliva, and malaria parasite genomics. No human genetic studies are planned in this study. However, any biological specimens remaining after analyses described in this study will be stored indefinitely for future studies unless the participants opt out during the informed consent process. Contact information of the study team is provided in the consent form to study participants, who can remove themselves from this study and any future studies that may use their blood samples at any time without penalty or prejudice.

## Statistical methods

### Statistical methods for primary and secondary outcomes {20a}

The intention-to-treat (ITT) analysis is the primary analysis approach for both the primary and secondary outcomes, and the per-protocol analysis will be included as a supplementary analysis.

The primary outcome of the study is malaria prevalence by microscopy in schoolchildren (3 to 15 years old) 12 months after Olyset®Plus ceiling net installation. The results of microscopic examination from the cross-sectional survey 12 months after the implementation will be compared between the intervention arm and the control arm, based on cluster-level summaries using the two-stage procedure [27]. In the first stage, an individual-level logistic regression model will be constructed with adjustments for confounders, including age, gender, bed net use, house structure, and SES, and a fitting value will be summarized for each cluster using the model. In the second stage, a residual from the fitted values and the observed values for each cluster will be computed. The difference between the two groups will be tested using Wilcoxon’s rank-sum test by ranking cluster-level summaries.

As a secondary outcome, the malaria prevalence by PCR and anemia prevalence at 6 and 12 months after the implementation will be evaluated similarly. The cumulative malaria incidence during the 12-month follow-up will be analyzed based on the cohort follow-up data. Both symptomatic disease incidence and infection incidence, including asymptomatic infection, will be compared between the intervention and control arm based on cluster-level summaries. Entomological parameters, namely anopheline mosquito density, species composition, infection rate, and antibodies (IgG) against Anopheles salivary proteins gSG6 and cE5 at 6 and 12 months post-installation, will be analyzed in the same manner. Community members’ perceptions are analyzed qualitatively based on the questionnaire, focus group discussion, and in-depth interviews.

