### Objectives {7}

The primary study objective is to determine the protective efficacy of Olyset®Plus ceiling nets in reducing malaria prevalence in children aged 3 to 15 years old, during a 12-month follow-up period.

The secondary objectives during a 12-month follow-up period are as follows: (1) to determine the total number of infections averted due to Olyset®Plus ceiling net by comparing the cumulative number of infections per person per year in cohort participants in the intervention and control arms; (2) to determine the protective efficacy of Olyset®Plus ceiling net in reducing anemia prevalence in children aged 3 to 15 years old; (3) to measure the impact of Olyset®Plus ceiling net on entomological parameters (anopheline mosquito density, composition, and malaria infection rate), (4) to measure the impact of the introduction of Olyset®Plus ceiling net on malaria preventive behavior, especially bed net usage after the 12 months of the intervention; and (5) to assess the acceptance of Olyset®Plus ceiling net within the community.

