### Interventions

#### Explanation for the choice of comparators {6b}

In Kenya, LLIN is the most widely used malaria preventive measure. The Division of National Malaria Programme coordinates free LLIN distribution, and the county governments deliver LLINs to residents in all endemic counties every 3 years. The primary purpose of this trial is to demonstrate the superiority in malaria prevention of adding Olyset®Plus ceiling nets to the standard LLIN. Thus, in the control arm, no Olyset®Plus ceiling nets will be installed. Free LLIN distribution and use will be allowed in the control and intervention arms as the current best practice. As for the planning stage, there is no plan for new LLIN distribution during the study period.

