### Outcomes {12}

The primary outcome of the study is malaria prevalence by microscopy in schoolchildren (3 to 15 years old) 12 months after Olyset®Plus ceiling net installation. The secondary outcomes are (1) malaria prevalence by PCR in schoolchildren at 6 and 12 months post-installation; (2) cumulative malaria incidence in the prospective cohort for 12 months post-installation; (3) anemia prevalence in schoolchildren at 6 and 12 months post-installation; (4) prevalence and level of antibodies (IgG) against *Anopheles* salivary proteins gSG6 and cE5 in the prospective cohort at 6 and 12 months post-installation, as a measure of exposure to mosquito bites; (5) anopheline mosquito density, species composition, and sporozoite infection prevalence at 6 and 12 months post-installation; (6) the percentage of cohort participants who sleep under the bed net at 6 and 12 months post-installation; and (7) perception of the Olyset®Plus ceiling nets among community members.

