##### Community census

After community sensitization and affirmation of agreement to participate provided by village chiefs, a census will be conducted by CHVs and experienced local research assistants to enumerate and record demographic information from all households in the health units that are receptive to our study. The following information will be collected from each household: (1) the number of residents; (2) the age, gender, and occupation of each resident; (3) the name of the school attended by each child; (4) the number, type, size, and functions of house structures; (5) the current LLIN ownership and usage; and (6) the GPS coordinates of the household. Written informed consent to participate in the ceiling net trial will be sought from the head of each household during census house visits.

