This study has several limitations. First, the visible nature of the ceiling net makes it impossible to blind study participants and field research staff. However, microscopists and laboratory technicians who process and analyze samples are blinded to the study arm assignment of participants. Indoor resting mosquitoes will be collected by pyrethrum spray catches and CDC light traps to determine vector density, which should be free of assessor bias. Second, since we hypothesize that schoolchildren will benefit the most from the additional protection of the ceiling net, our primary outcome is the prevalence of *Plasmodium* infections in children aged 3 to 15 years old. This will be assessed by school-based cross-sectional surveys. However, the benefit of the ceiling net will likely be extended to other age groups who share the same dwelling units. While we plan to examine the impact in a longitudinal cohort, the present cohort is small relative to the scale of the intervention. As such, findings in this cohort may not be generalizable to the trial population. Third, given that the ceiling nets are visible and thought to function in ways similar to conventional LLIN, it is conceivable that participants in the intervention arm may lower their usage of conventional LLIN, effectively relying on the ceiling net as a replacement rather than an addition to conventional LLIN for malaria protection. Continuous community engagement throughout the trial period will help to reinforce the importance of consistent LLIN use. Bi-weekly interviews with cohort participants will provide data on the pattern of LLIN use after ceiling net installation. We will conduct surveys and in-depth interviews to elicit participants’ perceptions of the ceiling net, which can guide future messaging and implementation.

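### The primary model adjusts for bed net use without saying when it is measured; a value taken after installation would be a mediator, and the result would no longer be the total effect of adding ceiling nets

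*Protocol article*

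**What the plan says.** Section {20a} sets out a two-stage analysis of the 12-month school survey. Stage one is specified as follows: "an individual-level logistic regression model will be constructed with adjustments for confounders, including age, gender, bed net use, house structure, and SES". In the second stage, fitted and observed values are compared by cluster: "The difference between the two groups will be tested using Wilcoxon’s rank-sum test by ranking cluster-level summaries". PCR and anemia prevalence are to be evaluated in a similar way. The same section states that "The intention-to-treat (ITT) analysis is the primary analysis approach for both the primary and secondary outcomes", and section {6b} gives the aim as to "demonstrate the superiority in malaria prevention of adding Olyset®Plus ceiling nets to the standard LLIN".

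Three other places treat bed net use as something the intervention may alter:
- Objectives {7}, secondary objective 4: "to measure the impact of the introduction of Olyset®Plus ceiling net on malaria preventive behavior, especially bed net usage".
- Outcomes {12}, secondary outcome 6: "the percentage of cohort participants who sleep under the bed net at 6 and 12 months post-installation".
- Discussion, limitations: "it is conceivable that participants in the intervention arm may lower their usage of conventional LLIN", so that the ceiling net replaces the LLIN instead of adding to it.

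A value from before allocation also exists. The community census collects "the current LLIN ownership and usage" from each household. Section {18a} links class rosters to that census.

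**The concern.** A confounder in a randomized comparison has to be fixed before allocation. Net use recorded at the 12-month survey is not: households that have received a ceiling net may stop hanging their LLIN. Such a variable lies on the path from allocation to infection.

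The aim in section {6b}, analysed by intention to treat, is a total effect. It includes whatever the ceiling net does to LLIN use. If intervention children sleep under LLINs less often and become infected for that reason, those infections are part of the result. A model that adjusts for current net use raises the expected prevalence in the intervention arm to allow for its lower use, and so sets those infections aside. The error would usually favour the intervention, and it would appear in just the situation that the limitations section raises.

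The wording of {20a} permits this analysis. It does not require it.

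**Working it through.** **1. The plan's own figure.** Section {14} gives 10 clusters per arm for 20% versus 8%, ICC 0.063, 150 children per cluster, power 0.8 and two-sided 5%.
- Individually randomized size (pooled variance): 131 per arm.
- Design effect: 1 + (150 − 1) × 0.063 = 10.387.
- Clusters: 131 × 10.387 / 150 = 9.07, rounded up to 10.

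The figure reproduces. Nothing in this point or its fix changes it.

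**2. Which net-use values are documented for the surveyed children?**

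| Source | Timing | Population |
|---|---|---|
| Community census | Before allocation: consent is sought at census visits, and Table 2 puts consent at week −8 and allocation at week 0 | All households in participating health units; linked to pupils through class rosters |
| Bi-weekly interviews; secondary outcome 6 | After installation | Cohort only |
| School survey, section {18a} | – | No bed net question is named |

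The only documented source for the primary-outcome population is therefore the census, but {20a} does not cite it.

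**3. Size of the distortion if the survey-time value is used.** From the plan: control prevalence 20%. Assumed, because the documents give no figures: control net use 80%, net-use odds ratio 0.5, direct ceiling-net odds ratio 0.5 or 0.7 (the effect at fixed net use), equal arms.

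*Step a, control arm.* Solve 0.8 × p(user) + 0.2 × p(non-user) = 0.20 with an odds ratio of 0.5. This gives p(user) = 0.1754 and p(non-user) = 0.2984. Check: 0.1403 + 0.0597 = 0.2000.

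*Step b, intervention arm, direct odds ratio 0.5.* Halving the odds gives p(user) = 0.0961 and p(non-user) = 0.1754. If use falls to 60%, prevalence is 0.6 × 0.0961 + 0.4 × 0.1754 = 0.1278. Total efficacy = 1 − 0.1278/0.20 = 36.1%.

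*Step c, first stage (net use, no arm term).* The fitted values are the pooled prevalences:
- users: (0.8 × 0.1754 + 0.6 × 0.0961)/1.4 = 0.1414
- non-users: (0.2 × 0.2984 + 0.4 × 0.1754)/0.6 = 0.2164

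*Step d, observed over expected.*
- Control expected: 0.8 × 0.1414 + 0.2 × 0.2164 = 0.1564; ratio 0.20/0.1564 = 1.279.
- Intervention expected: 0.6 × 0.1414 + 0.4 × 0.2164 = 0.1714; ratio 0.1278/0.1714 = 0.746.
- Adjusted efficacy = 1 − 0.746/1.279 = 41.7%.

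The same steps for other falls in use:

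| Fall in use (points) | Direct OR | Total efficacy | Adjusted efficacy |
|---|---|---|---|
| 0 | 0.5 | 44.0% | 44.0% |
| 5 | 0.5 | 42.0% | 43.7% |
| 10 | 0.5 | 40.0% | 43.2% |
| 20 | 0.5 | 36.1% | 41.7% |
| 5 | 0.7 | 22.7% | 25.0% |
| 10 | 0.7 | 20.2% | 24.7% |
| 30 | 0.7 | 10.2% | 22.3% |

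The first row also stands for a pre-allocation covariate that is balanced between arms: there is no distortion.

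**4. Effect on the test.** The two-stage procedure was simulated with 10 clusters of 150 per arm, a cluster SD of 0.63 on the logit scale (roughly the planned ICC), control net use assumed at 70%, net-use odds ratios of 0.7, 0.5 and 0.3, and 1500 runs per scenario. With a true total effect of nil, the Wilcoxon test without net use rejected in 4–6% of runs. Adjusted for post-installation use, rejection was 4–6% when intervention use fell to 60%, 4–9% at 50% and 4–17% at 30%. The 17% needs both the largest fall and the strongest net effect.

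With a true ratio of 0.40, the adjusted ratio ran from 0.33 to 0.42. In one scenario (use 30%, odds ratio 0.7) it was 0.415 against 0.398 unadjusted, a slight understatement. This can happen because the first-stage model has no arm term, so the net-use coefficient absorbs part of the arm effect. The direction is usual, not universal.

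**The case against.** A reader might infer that the primary analysis will adjust for a mediator, and that the plan expects LLIN use to fall. The documents support neither.

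On the first, {20a} gives no date. The only net-use source documented for the surveyed children precedes allocation, and the covariate is listed beside age and gender as a confounder, which fits a baseline reading. Adjusting for that value leaves the total effect intact. On the second, the limitations section calls substitution only conceivable, the plan encourages continued LLIN use in both arms, and objective 4 and outcome 6 commit to measuring net use without predicting a change. It is also fair that the distortion is about 2 to 4 or 5 percentage points for a 5- to 10-point fall, and that a condensed article may leave the dating of covariates to an analysis plan.

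All of that stands, and it makes the point conditional. It does not remove it. This document names the covariate itself and calls it a confounder. The census is taken household by household, while the covariate sits in an individual-level model of survey data. Enrollment closed in October 2021 and the cross-sectional survey was completed in February 2023, so an analyst could easily prefer current use. That the school-survey description names no bed net question does not show that none was asked.

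**Conclusion.** The point holds in conditional form. Section {20a} leaves open when bed net use is measured, and one permitted reading conflicts with the intention-to-treat aim of section {6b} and with the plan's own treatment of net use as a possible effect of the intervention. With the pre-installation value there is no such bias. With the survey-time value the primary comparison is not the total effect and will usually overstate the benefit if LLIN use falls in the intervention arm.

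Under the assumptions above, the overstatement is nil with no fall, 3.2 points for a 10-point fall, 5.6 points for a 20-point fall (direct odds ratio 0.5) and 12.1 points for a 30-point fall (direct odds ratio 0.7). Material inflation of the test's error rate needs a large fall together with a strong LLIN effect. Control net use, the fall and both odds ratios are assumed; only the 20% prevalence is the plan's. The point deserves settling because it concerns the primary result and costs almost nothing.

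**What to change.** In {20a}, state that the bed net covariate is LLIN ownership or usage as recorded in the pre-installation census, linked to each child through the class rosters. Alternatively, drop it from the primary model. Make the same choice for the PCR and anemia models that follow the same method. Report any adjustment for net use at the time of the survey only as a labelled exploratory analysis. Settle this before arm-level results are seen.

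The cost is one clause. No new data are needed, and the 10 clusters per arm are unaffected. The downside is that the census value may exist only at household level and may predict infection at 12 months somewhat less well than current individual use.

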### Trial design {8}

The study is a cluster-randomized controlled trial with 10 clusters per arm (intervention and control), consisting of two cross-sectional school surveys after 6 months and 12 months of intervention and one cohort followed for 12 months in both arms. Each cluster is a health unit comprising approximately 100 households, including 500 individuals. Each health unit has an assigned community health volunteer (CHV) responsible for national health surveys and routine community health activities. This study also utilizes CHVs as messengers of study-related information and enumerators of the questionnaire surveys.

To evaluate the primary outcome, 150 schoolchildren will be recruited from each cluster. To evaluate the protective efficacy in reducing the cumulative incidence, 25 individuals will be recruited from each cluster and followed up for 12 months as a cohort. Residents of all age groups will be recruited to allow for the evaluation of the impact on asymptomatic and/or submicroscopic infections, which are also observed in adults. Cohort participants will be interviewed about their health conditions every 2 weeks by CHVs and are asked to provide a blood sample to monitor asymptomatic infection. The blood collection will be done by finger prick and venipuncture alternately. Five house structures in each cluster will be randomly selected and subjected to pyrethrum spray catches (PSC) for the entomological assessment. The mosquito sampling will be implemented 6 and 12 months after the intervention. Sampling will take place at the same structures at both time points.

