#### Sample size {14}

Parasite prevalence by microscopy among schoolchildren on Mfangano Island is approximately 20%, based on our previous study [26]. To detect the expected effect of 60% parasite prevalence reduction (to a prevalence of 8%) relative to control, with a power of 0.8, two-sided type 1 error of 5%, an intraclass correlation coefficient (ICC) for clusters of 0.063 (estimated based on our previous school study by assuming each school as a cluster), and average cluster size 150 (number of schoolchildren), the required number of clusters is 10 (or 1500 children) per arm using Stata/MP16.1. Based on the 2019 national census, children 3 to 15 years old account for 40.3% of the total population in Homa Bay County. The study requires a total population (all ages) of 7444 people or 1880 households (mean of 3.96 persons per household on Mfangano). By assuming a 3% dropout per month, we plan to enroll 1315 households for the intervention arm.

For the longitudinal cohort, we estimate the infection incidence on Mfangano Island as approximately 2.0 per person-year based on the data on Kenya Health Information System (KHIS). To detect the expected effect of a 40% reduction (1.2 per person-year), with a power of 0.8, two-side type 1 error of 5%, and an average cluster size of 25 individuals, the required number of clusters is 7 (or 350 individuals) per arm based on Eq. 7.3 on reference [27]. Assuming 3% of cohort participants will drop out per month, we plan to enroll 490 individuals in the cohort.

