#### Concealment mechanism {16b}

Each cluster is assigned a computer-generated random number. The random numbers are then arranged in ascending order. Clusters with random numbers in the smaller half are assigned to the intervention arm, while those in the larger half are in the control arm.

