### Data collection and management

#### Plans for assessment and collection of outcomes {18a}

##### Cross-sectional school surveys

Malaria prevalence in children will be estimated using cross-sectional malariometric surveys in schools. These surveys will be conducted at baseline (before ceiling net installation), 6 months, and 12 months post-installation. In addition, class rosters will be cross-referenced with the community census to determine the allocation of each eligible student in the trial clusters.

Malaria status will be determined using three methods: RDT, microscopy, and PCR. First, a finger prick blood sample will be collected for on-site diagnosis by Paracheck-Pf® RDT (Orchid Biomedical Systems, India). Survey participants with positive test results will receive a treatment course of artemether-lumefantrine with dosing instructions as per the guidelines from the Ministry of Health in Kenya. Blood smears will be prepared on-site and transported to the main laboratory in Homa Bay, where thin smears are fixed with methanol. All smears are stained with 3% Giemsa solution for 30 min, then examined by experienced microscopists. Two blood samples (70 µl each) will be collected with a 75-mm EDTA-coated micro-hematocrit capillary tube (Marienfeld, Lauda-Königshofen, Germany) and spotted on Whatman ET31 Chr filter paper (Whatman International. Maidstone, UK). The blood spots will be allowed to dry at ambient temperature and stored in individual zipped plastic bags at − 20 °C. The dried blood spots (DBS) will be used for DNA extraction and determination of malaria status by PCR [28].

Hemoglobin (Hb) levels will be measured using the HemoCue Hb 801 Analyzer (HemoCue, Ängelholm, Sweden). Survey participants with severe anemia based on the WHO criteria [29] will be referred to local health facilities for further consultation.

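### Baseline cluster malaria prevalence is collected but not named in the primary adjustment; pre-specifying it would be a cheap improvement, with a gain that depends on an undocumented correlation

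*Protocol article*

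**What the plan says.** The protocol article, under Statistical methods {20a}, compares 12-month microscopy prevalence between arms by a two-stage procedure. An individual-level logistic model is fitted "with adjustments for confounders, including age, gender, bed net use, house structure, and SES". Cluster residuals are then formed and compared by Wilcoxon's rank-sum test. PCR prevalence and anemia are analysed in the same way.

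On the school surveys, the section on data collection states: "These surveys will be conducted at baseline (before ceiling net installation), 6 months, and 12 months post-installation". Malaria status is determined by RDT, microscopy and PCR, hemoglobin is measured, and class rosters are matched to the census to place each child in a trial cluster. Table 2 also marks a school survey at week 0. No section gives the baseline survey a role in the comparison of arms.

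The design is a "cluster-randomized controlled trial with 10 clusters per arm (intervention and control"). Allocation sorts the clusters by random number: "Clusters with random numbers in the smaller half are assigned to the intervention arm". The other half become controls. No stratification, matching or constraint on prevalence is stated.

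**The concern.** With 10 clusters per arm and an unrestricted split, the arms can differ by chance in underlying transmission. The best available measure of that is each cluster's prevalence before installation, by the same method as the primary outcome. The protocol plans to collect it but does not name it among the adjustment variables. The covariates that are named describe individuals and households, and may capture little of the difference in transmission between one health unit and another. At stake is precision in a trial with power close to 0.80, and how credible the result would be if the arms turned out visibly unequal at baseline. Because the list is open, adding baseline prevalence after the results are known would look like a data-driven choice.

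**Working it through.** **Inputs from Sample size {14} and Trial design {8}.** Control prevalence p1 = 0.20 ("Parasite prevalence by microscopy among schoolchildren on Mfangano Island is approximately 20"%); intervention prevalence p2 = 0.08 ("expected effect of 60% parasite prevalence reduction (to a prevalence of 8"%); "with a power of 0.8, two-sided type 1 error of 5%, an intraclass correlation coefficient (ICC) for clusters of 0.063"; 150 children per cluster; 10 clusters per arm. The ICC was "estimated based on our previous school study by assuming each school as a cluster".

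**The plan's own figure.** Individual randomisation with pooled variance needs 131 children per arm. The design effect is 1 + 149 × 0.063 = 10.387. Then 131 × 10.387 / 150 = 9.07, which rounds up to 10 clusters per arm. The stated figure reproduces.

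**Where the variance lies.** For one cluster at p = 0.20, p(1 − p) = 0.16.
- Between clusters: 0.063 × 0.16 = 0.01008.
- Within clusters: 0.937 × 0.16 / 150 = 0.00100.
- Between-cluster share: 0.01008 / 0.01108 = 0.91. The share is the same at p = 0.08.

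**Chance imbalance at baseline.** The SD of the difference in mean baseline prevalence between arms is √(2 × 0.01108 / 10) = 0.047, or 4.7 percentage points (assuming 150 children per cluster at baseline too). By the normal approximation, a difference above 5 points in either direction has probability about 0.29. A difference above 6 points, half the planned 12-point effect, has probability about 0.20.

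**Unadjusted power.** With p2(1 − p2) = 0.0736, the variance summed over the two arms is 0.063 × 0.2336 + 0.937 × 0.2336 / 150 = 0.01472 + 0.00146 = 0.01618. The SE is √(0.01618 / 10) = 0.0402. Non-central t power for a difference of 0.12 on 18 df is 0.805.

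**Power with regression on arm and baseline prevalence (17 df).** Let r be the correlation between the underlying baseline and 12-month cluster prevalence. The documents do not give it, so 0 to 0.7 is an assumed range. The observed baseline carries sampling error, so the between-cluster part is multiplied by 1 − 0.91r². With 20 clusters, chance imbalance in the covariate itself inflates the variance by about 17/16 on average.

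| r | Variance: (0.01472 × (1 − 0.91r²) + 0.00146) × 17/16 | SE | Power |
|---|---|---|---|
| 0 | 0.01719 | 0.0415 | 0.78 |
| 0.3 | 0.01591 | 0.0399 | 0.81 |
| 0.5 | 0.01363 | 0.0369 | 0.865 |
| 0.7 | 0.01022 | 0.0320 | 0.94 |

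Leaving out the 17/16 factor would give 0.83, 0.88 and 0.95 at r = 0.3, 0.5 and 0.7, which is slightly optimistic.

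**Simulation.** Clusters were drawn from beta-binomial distributions with the plan's prevalences and ICC, with baseline entered as a linear cluster-level term.

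| r | Rank-sum, unadjusted | Rank-sum on residuals adjusted for baseline | Regression on arm and baseline |
|---|---|---|---|
| 0 | about 0.82 | 0.77 | 0.79 |
| 0.3 | about 0.82 | 0.80 | 0.82 |
| 0.5 | about 0.82 | 0.85 | 0.87 |
| 0.7 | about 0.82 | 0.91 | 0.94 |

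Repeat runs differ by up to about 2 points. At r = 0.7, type I error was about 0.04 to 0.045 for the adjusted rank-sum test and 0.05 for the regression.

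**The case against.** The strongest reply is that this is a preference about efficiency. The two-stage residual method is recognised and remains valid under randomisation with no baseline covariate, and the trial reaches its target power without one. That stands.

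A reader might infer that the 4.7-point SD is uncontrolled bias. It is not. It is ordinary sampling variation between clusters, which the sample size allows for through the ICC and which the cluster-level test carries in its error. It matters only conditionally: in a trial where the draw is unequal, adjustment would bring the estimate closer to the truth.

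A reader might also infer that baseline prevalence has been excluded. The text does not say so. The list is open, and a final covariate list may sit in an analysis plan that is not shown. Still, section {20a} names five covariates for the primary model and section {31c} describes the article as the full protocol, so recommending a sixth addresses a stated choice and not an omitted detail.

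Nor is a gain in precision assured. It depends on r, and at low r adjustment costs power. Regressing cluster residuals on arm and baseline would also replace the planned rank-sum test with a parametric model on 20 points, which is more than adding a covariate.

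Two further limits stand. That every cluster has a usable baseline value is inferred from the roster-census link, since no baseline numbers per cluster are given and Trial design {8} lists only the 6- and 12-month surveys. And Trial status reports the cross-sectional surveys complete in February 2023, so any change now follows data collection.

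**Conclusion.** The point holds as a cheap improvement, not as an error. The planned primary analysis is valid, with power of about 0.80 for 20% against 8%. Baseline cluster prevalence is not named in an open adjustment list, although the trial plans to measure it and about 91% of the variance of a cluster summary lies between clusters. With the regression, adjustment breaks even at about r = 0.3 and gains about 5 points of power at r = 0.5 and about 12 at r = 0.7. With the rank-sum test kept, the gain is about 3 points at 0.5 and 9 at 0.7, with a loss of about 2 points at 0.3. These figures rest on the plan's prevalences and ICC, 150 children per cluster at both surveys, and an assumed range for r.

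**What to change.** Before arm is linked to the 12-month results, replace the open list with a closed one that includes each cluster's baseline microscopy prevalence. Use baseline PCR prevalence for the PCR outcome and baseline anemia prevalence for the anemia outcome. Then choose one route and state it:

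- Enter baseline prevalence in the covariate adjustment that produces the cluster residuals, and keep the rank-sum test as primary.
- Regress the cluster residuals on arm and baseline prevalence (17 df), and state that this replaces the rank-sum test as the primary test.

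If a correlation between surveys can be estimated from earlier data on the island, report it in support of the choice. Because data collection is complete, date the decision and record that the analysts were still blinded, as section {17a} intends.

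No new data are needed. The cost is one degree of freedom, a loss of about 3 to 5 points of power if r is near zero (the larger figure with the rank-sum test kept), and a change of primary test under the second route.
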